### Intervention: 0Phobia

0Phobia consists of six animated cognitive behavioral therapy (CBT)-based modules. The home screen (Fig. 2) features the six modules, each of which is consecutively unlocked, a “watch again” menu in which each of the instructions can be watched again, a menu providing access to the VR environment, and a “My 0Phobia” menu where participants can view the goals they have set for themselves for the intervention, their dysfunctional and functional thoughts, and their anxiety hierarchy for practicing in the real world.

**Fig. 2 Fig2:**
[figure not shown]
Screenshots of 0Phobia

**Fig. 3 Fig3:**
[figure not shown]
Standard Protocol Items: Recommendations for Interventional Trials (SPIRIT) schedule for enrollment, interventions and assessments

Participants will follow the modules according to their own tempo and timing. Each module modules takes between 5 and 20 min to complete (see Table 1). The CBT content in the modules is provided by a virtual therapist using 2D animations and a voice-over (Fig. 2). The virtual therapist, “Tara,” guides the participant through the intervention and provides case examples in the form of a returning character, “Louise,” a theater manager who has overcome her own acrophobia (Fig. 2). Over the course of the modules Tara describes to Louise how her phobia emerged and developed, what the consequences were for her and how she resolved it (i.e., through exposure therapy and repeated practice, see Fig. 2). Louise also motivates the user to continue with 0Phobia.

**Table 1 Tab1:** Overview of 0Phobia modules

Modules	Contents
1. Psychoeducation	Explanation of the nature of a specific phobia, its emergences and potential consequences
2. Goals and treatment principles	Participants define their goals for the treatment and treatment principles underlying exposure are explained
3. Exposure therapy	Virtual reality (VR) content will be explained and participants will practice in a virtual environment
4. Cognitive therapy	According to the established principles of cognitive behavioral therapy (CBT), users identify and evaluate their automatic catastrophic thoughts regarding heights (e.g., “I am bound to fall” or “I will jump”). After that, subjects can practice with non-interactive 360° VR videos
5. Cognitive therapy	In this module, users will develop helping thoughts countering the automatic catastrophic thoughts identified in module 4
6. The next steps..	This module contains information on how the user can continue their practice and further reduce their fear and prevent relapse. This includes developing an individualized fear hierarchy. Explicit attention is devoted to motivation and encouragement

Aside from the 2D animated environment, the intervention consists of a gamified immersive VR environment. From module 3 onwards, participants start to practice with exposure in the virtual environment, parallel to completing the remaining modules. The virtual environment is a gamified theater setting and within the story of the game, the participant is replacing Louise as the theater manager (see Fig. 2). To prepare the theater for the night’s performance, participants need to complete a number of assignments in the theater. Each of these assignments involve different levels of exposure to heights (from standing on a small ladder to standing on a ledge high above the stage). By looking at assets located on the theater floor that need to be collected, participants are encouraged to look down and face their fears.

Aside from the virtual theater, 0Phobia also contains four 360° videos that are also watched with the VR goggles in which participants stand on the top of a high building, cross a high suspension bridge, sit on a rooftop with their legs dangling over the edge, or stand on a high crane. In conjunction, the various virtual environment and 360° videos cover the entire exposure spectrum, from very-low- to very-high-intensity exposure. Based on the fear levels and performance the user receives feedback. When users rate their fear levels using a stare function in VR below a score of 3 on a 10-point scale, an automated feedback pops up mentioning that they can continue to the next level. When users rate their anxiety level between 4 and 7, they are advised to practice the same level again. When rated an anxiety level between 8 to 10, they need to practice the same level again before commencing to the next level. Subjects can return to practicing in VR as often as they like and gradually expose themselves to different heights and fear intensities. Although the importance of exposure in VR is stressed out in the 2D animations and participants are encouraged to practice in VR, participants can skip VR exposure and proceed to the next module, because for some people, fear levels may still be too high. After evaluating their automatic anxiety evoking thoughts, they can practice in VR exposure. Only during the exposure sessions will participants use the cardboard goggles.

Participants will have access to the mobile app after post test and follow-up. Usage data during this period will be collected. 0Phobia has been extensively user-tested throughout development process and modified according to user-feedback.

### Assessments

#### Primary outcome measure

##### Acrophobia questionnaire

The main outcome measures will be the 20-item anxiety subscale and the 20-item avoidance subscale of the Acrophobia Questionnaire (AQ; [28]). The AQ is a widely-used instrument with good psychometric properties [28]. The anxiety subscale is measured using a 7-point Likert scale (0 = not anxious to 6 = extremely anxious), total score range 0–120. The avoidance subscale uses a 3-point Likert scale (“I would not avoid it” to “I would not do it under any circumstances”). Both subscales will be taken at baseline, directly after finishing the modules, at post test, and at follow-up. See Fig. 3. 

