**Methods/design:**

Participants (*N* = 180, aged 18–65 years) with acrophobia symptoms will be recruited from the Dutch general population and randomized to either 0Phobia (*n* = 90) or a waitlist control condition (*n* = 90). 0Phobia will be delivered over a period of 3 weeks and includes psychoeducation, VR exposure, cognitive techniques, monitoring of symptoms, and relapse prevention. The primary outcome measure will be the Acrophobia Questionnaire. Secondary outcome measures will include user-friendliness, symptoms of anxiety, depression, and mastery. Assessments will take place online at baseline, directly after the intervention (post test) and at follow-up (3 months).

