### Sample size

The primary outcome measure, the AQ, has been used for the power calculations. In previous RCTs using the AQ as an outcome measure, effect sizes of 0.79–1.42 [14, 15] were demonstrated. However, as the present intervention will use low-end cardboard VR goggles instead of expensive head-mounted displays, the current study uses a more conservative estimate for the post-treatment effect on the AQ. In order to detect a difference between the experimental and the waitlist control condition with a standardized effect size (Cohen’s d) of 0.50 (two-sided), an alpha of 0.05 and statistical power (1 − *β*) of 0.80, we need 64 participants in each condition (128 participants in total). With an anticipated dropout of 40%, this requires a total target sample size of 180 participants.

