### Analyses

#### Statistical analyses

The primary outcome measure (AQ; [28]) and secondary study parameters (ATHQ, PHQ, IPQ, SUS, BAI, and Pearlin Mastery Scale) will be treated as continuous outcomes. Continuous variables will be presented as mean, standard deviation, and minimum and maximum number of observations. Categorical variables will be presented in terms of frequencies and percentages. Descriptive statistics of demographics and clinical outcomes will be compared between the experimental and the waitlist condition.

To assess whether attrition is non-random, we will construct a balancing table for background characteristics, pre-scores and other covariates in which participants with and without missing outcome observations are compared. Potential implications of non-random sample attrition on the observed treatment estimates will then be assessed by estimating treatment effect bounds for samples with non-random sample selection/attrition as proposed by Lee [47]. Using this approach we are able to infer whether observed differences between the intervention and control groups can be explained by extreme, non-random sample selection. Depending on these results, missing outcome observations for participants will be imputed based on pre-scores and a set of background characteristics. The quantitative analysis of the primary and secondary endpoints will be performed on an intention-to-treat (ITT) basis following the per-protocol analysis. The primary analysis will be based on ITT. Potential dependency between outcome measures is addressed using multivariate analyses. Potential heterogeneity will be addressed by estimating treatment effects for subgroups (e.g., based on pre-scores). In order to understand the mechanisms by which observed differences are generated, a rich set of analyses is performed based on variation in (1) experiences when using the app (e.g., perceived user friendliness, ecological momentary assessment, cybersickness, VR vs 360°) and (2) intensity of using the app. Per-protocol analysis will be based on two groups: (1) those who returned the post-test and follow-up questionnaires (completers) and (2) those who completed 50% or more of the treatment modules and returned the questionnaires (adherent completers). Comparisons will be made between and within the groups before and after measurements.

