Intention-to-treat and per-protocol analysis will be used on continuous scales using regression estimation standardized effect sizes (Cohen’s *d*) and confidence intervals will be calculated. Usage data through the mobile app (anxiety level during VR exposure, time spent in VR, number of VR sessions completed) will be collected during the study to model missing data. SPSS version 21 will be used for the analyses. A *p* value < 0.05 will be considered to indicate statistical significance. All design, implementation, and reporting will be carried out in accordance with Consolidated Standards of Reporting Trials (CONSORT) and Standard Protocol Items: Recommendations for Interventional Trials (SPIRIT) guidelines (Additional file 1) [48–50].

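### The protocol names two main outcome measures in one place and a single primary outcome elsewhere, so the stated 5% error rate and 80% power are not tied to a defined endpoint

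*Protocol article*

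**What the plan says.** The protocol article describes the primary outcome in four places.

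- **Assessments, Acrophobia questionnaire** (under a singular primary outcome heading): "The main outcome measures will be the 20-item anxiety subscale and the 20-item avoidance subscale of the Acrophobia Questionnaire". Anxiety is rated on a 7-point scale with a total of 0 to 120, and avoidance on a 3-point scale. No score combining the two is described.
- **Abstract, Methods/design:** "The primary outcome measure will be the Acrophobia Questionnaire".
- **Sample size:** "The primary outcome measure, the AQ, has been used for the power calculations". This is one comparison "with a standardized effect size (Cohen’s d) of 0.50 (two-sided"), with "an alpha of 0.05 and statistical power" of 0.80, giving 64 per arm. Neither subscale is named.
- **Statistical analyses:** "The primary outcome measure (AQ; [28]) and secondary study parameters" are to be treated as continuous. Again neither subscale is named.

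Two further sentences under Statistical analyses bear on testing. On the threshold, a p "value < 0.05 will be considered to indicate statistical significance". On several outcomes, "Potential dependency between outcome measures is addressed using multivariate analyses".

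The inclusion criteria use AQ-Anxiety alone to set eligibility.

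**The concern.** One section names two outcomes and three treat the AQ as one. The two subscales have different response formats, and no combined score is defined that would turn them into a single endpoint. A reader of the eventual report could not tell from the protocol whether the powered claim concerned anxiety, avoidance, or both together.

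The choice affects the error rates. If either subscale is enough, two chances at 0.05 give a primary claim with more than a 5% false-positive rate. If both are required, the false-positive rate is safe, but a calculation made for one comparison overstates the chance of success. On neither two-outcome reading do alpha 0.05 and power 0.80 hold together for the primary claim.

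**Working it through.** **Inputs from the protocol article:** d = 0.50, two-sided alpha 0.05, power 0.80, 64 per arm (Sample size); two main subscales (Acrophobia questionnaire); threshold 0.05 (Statistical analyses).

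**Assumptions, because the documents give no figure:** the correlation rho between the two subscales within arm, which is also the correlation of their test statistics, shown over a range; and, for the both-required case, d = 0.50 on each subscale.

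**1. The plan's own figure.** The normal approximation gives n = 2 × (1.960 + 0.842)² / 0.50² = 62.8, so 63 per arm. The two-sample t-test gives 63.77, so 64, and its power at 64 per arm is 0.801. The stated 64 is reproduced, for one comparison.

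**2. Either subscale counts as success.** With both null hypotheses true, the false-positive rate is 1 − P(|Z1| < 1.96 and |Z2| < 1.96), where (Z1, Z2) is bivariate normal with correlation rho. At rho = 0 this is 1 − 0.95² = 0.0975, the maximum.

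| rho | at least one p < 0.05 |
|---|---|
| 0 | 9.75% |
| 0.3 | 9.5% |
| 0.5 | 9.1% |
| 0.7 | 8.4% |
| 0.8 | 7.8% |
| 0.9 | 7.0% |
| 1 | 5.0% |

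Counting only errors that favour the intervention, the rate is 4.9% at rho = 0, 4.5% at 0.5 and 4.2% at 0.7, against a nominal 2.5%.

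**3. Both subscales must be significant.** The false-positive rate is at most 5%. For power, each test statistic has mean 0.50 / √(2/64) = 2.83, which exceeds 1.96 by 0.87. Each test alone therefore has power 0.807 (normal approximation), and joint power is P(both exceed 1.96).

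| rho | power, both significant, 64 per arm |
|---|---|
| 0 | 0.807² = 0.652 |
| 0.5 | 0.697 |
| 0.7 | 0.722 |
| 0.8 | 0.738 |

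**4. A joint test as a gate.** Suppose the subscales could be tested only after a joint test of both is significant at 0.05. If both nulls are true, any claim needs the joint test to reject, so the rate is at most 5%. If only one null is true, a false claim needs that subscale's own 0.05 test to reject, so again at most 5%. With two hypotheses this is a closed procedure and needs no further adjustment. The protocol's sentence on multivariate analyses does not say which outcomes enter, which test is used, or whether it must be passed first.

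**The case against.** There are three fair points on the other side.

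**The analysis plan is not shown.** A success rule and a multiplicity procedure are often left to it, and this is a journal article. Their absence alone would not be a finding. What stands is narrower: the article contradicts itself on whether there is one primary outcome or two, and the power statement depends on the answer.

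**The wording can be read charitably.** The three singular mentions may name the instrument, and the assessments section may then list its parts. That softens the contradiction but does not remove it. Without a combined score, naming the instrument still leaves two endpoints and one power calculation.

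**Multivariate analyses are promised.** As shown above, a joint test used as a gate would hold the rate at 5%. A reader might infer that the promised analyses cannot help because each subscale is still tested at 0.05; that would be wrong. The valid criticism is that no gate is stated.

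Other stronger readings also go beyond the documents:

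- A reader might conclude that the false-positive rate is 8% to 9%. That needs an either-subscale rule and a correlation, neither of which the protocol gives.
- A reader might add an AQ total as a third route to success. The only total described is the anxiety subscale's own (20 items × 6 = 120).
- A reader might compute power at the number left after dropout. That loss belongs to the dropout allowance and is a separate matter from having two outcomes.

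**Conclusion.** The point holds as a contradiction about the identity of the primary endpoint, with conditional consequences:

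- **If either subscale suffices**, the false-positive rate for the primary claim is above 5% (for any correlation short of 1) and at most 9.75%. It is about 9.1% to 7.8% for an assumed correlation of 0.5 to 0.8.
- **If both are required**, the false-positive rate is controlled but power at 64 per arm is about 70% to 74%, not 80%, assuming d = 0.5 on both subscales and the same correlations.
- **If one endpoint is meant, or a joint test is a gate**, the false-positive rate stays within 5%. The protocol states neither.

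This should be fixed. The size of any inflation is unknown and an unseen analysis plan may settle it, so the protocol does not establish that the error rate is in fact inflated.

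**What to change.** Before outcome data are analysed, in the protocol, the analysis plan and the registry entry:

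1. Name one primary endpoint, for example AQ-Anxiety at post test. It already sets eligibility, and post test is the last assessment before the waitlist arm receives the intervention.
2. Test AQ-Avoidance at 0.05 only if AQ-Anxiety is significant. This fixed sequence holds the overall rate at 5%.
3. State that alpha 0.05, 80% power and 64 per arm apply to that single endpoint at the assumed d = 0.5. The present text does not say which subscale the prior effect sizes refer to, so this should be written as a new, explicit assumption.
4. Make the abstract, sample size, assessments and analysis sections agree.

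The cost is a few sentences and no extra participants. The small downside is that avoidance can be claimed only after anxiety; on the assumptions above, the chance of claiming both is the same 70% to 74%.

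Other rules would also resolve the ambiguity. A gating joint test would do so if the outcomes and the test were named. Splitting alpha at 0.025 per subscale would hold the rate to at most 4.9%, but it needs 78 evaluable per arm (t-test) for 80% power on each, or leaves about 71% per subscale at 64. Requiring both subscales is also valid, provided the power statement is revised.

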#### Secondary outcome measures

##### Attitudes Towards Heights Questionnaire

The Attitudes Towards Heights Questionnaire (ATHQ; [33]), with minor modifications to the wording reported in [34] is a six-item measure in which individuals read pairs of dichotomous adjectives describing ways people may feel about heights (e.g., “Good/Bad,” “Safe/Dangerous”), and rate how they feel about elevated places on a scale of 0 (which corresponds with the first adjective) to 10 (which corresponds with the second adjective). The ATHQ has been used in several acrophobia treatment studies and is sensitive to treatment effects [34, 35]. The reliability is good [36]. This questionnaire will be completed at baseline, post test, and follow-up.

##### Beck Anxiety Inventory

The Beck Anxiety Inventory (BAI; [37]) is a 21-item self-report questionnaire assessing symptoms of anxiety. Participants record how much they have been bothered by each symptom during the past week, including the day the questionnaire is administered (4-point Likert scale ranging from 0 = not at all to 3 = severely: “I could barely stand it”). The total score ranges from 0 to 63. Internal consistency is high (0.90–0.94) and convergent validity is good [38]. This questionnaire will be completed at baseline, post test, and follow-up.

##### System Usability Scale

The System Usability Scale (SUS; [39]) will be used to measure the user-friendliness of the app. The SUS is composed of 10 statements that are scored on a 5-point Likert scale ranging from 1 = strongly agree to 5 = strongly disagree. Scores are converted to a new number, added up and then multiplied by 2.5 to convert the original scores to 0–100, with higher scores indicating better usability (for details, please see Bangor et al., 2008). This means that digital products that are at least passable have SUS scores above 68, with better products scoring in the high 70s to upper 80s. Truly superior products score above 90. Products with scores less than 70 should be considered candidates for increased scrutiny and continued improvement and should be judged to be marginal at best. Reliability of the scale is good [39]. This questionnaire will be completed at post test.

##### Igroup Presence Questionnaire

The Igroup Presence Questionnaire (IPQ; [40]) is a 14-item questionnaire which assess realism and “presence,” i.e., the subjective feeling of being immersed in the virtual environment. Each of the items has five response categories from 1 = fully disagree to 5 = fully agree. Internal consistency is adequate. This questionnaire along with some open questions about user experience of the VR environment will be completed at post test.

##### Mastery

The Pearlin Mastery Scale [41] is a seven-item scale to measure self-experienced control over a situation. Each of the seven items has five response categories ranging from 1 = totally disagree to 5 = totally agree. The questionnaire has good psychometric properties [41]. This questionnaire will be completed at baseline, post test, and follow-up.

##### Patient Health Questionnaire

The nine-item mood module of the Patient Health Questionnaire (PHQ-9; [42]) is used to screen subjects for depressive disorders. The nine items are each scored on a 4-point Likert scale ranging from 0 to 3 (total score range 0–27). Sensitivity and specificity coefficients are good [43]. This questionnaire will be completed at baseline, post test, and follow-up.

##### Ecological momentary assessment

Assessment of current anxiety level directly after exposure when using the 0Phobia app (one question: ‘How high was your anxiety at highest?’).

#### Additional measures

##### Professional treatment

Two items will be included in the screening, the post-test, and the follow-up measure assessing whether participants have attended professional treatment or received medication for their specific phobia right before (screening), during (post test), or after (follow-up) the 0Phobia study.

##### Cybersickness

Participants will rate the extent to which they experienced cybersickness while practicing in VR using three items adapted from the Simulator Sickness Questionnaire, (SSQ; [44, 45]), e.g., “How often did you experience any of the abovementioned symptoms while practicing in virtual reality” using a 3-point scale ranging from 0 (never) to 3 (always). Symptoms include eye strain, headache, pallor, sweating, dryness of mouth, fullness of stomach, disorientation, vertigo, ataxia, nausea, and vomiting [44]. This questionnaire will be completed at post test.

##### Vision impairment

Participants will be asked to report any potential vision impairments they have (e.g., wearing glasses, lazy eye, cataract, other). This questionnaire will be completed at post test.

##### Practice in real life

Two items will be used to determine the extent to which participants also practiced with height situations in real life. This questionnaire will be completed at post test and follow-up.

All assessments are programmed with Survalyzer software [46] (Fig. 3).

### Analyses

#### Statistical analyses

The primary outcome measure (AQ; [28]) and secondary study parameters (ATHQ, PHQ, IPQ, SUS, BAI, and Pearlin Mastery Scale) will be treated as continuous outcomes. Continuous variables will be presented as mean, standard deviation, and minimum and maximum number of observations. Categorical variables will be presented in terms of frequencies and percentages. Descriptive statistics of demographics and clinical outcomes will be compared between the experimental and the waitlist condition.

To assess whether attrition is non-random, we will construct a balancing table for background characteristics, pre-scores and other covariates in which participants with and without missing outcome observations are compared. Potential implications of non-random sample attrition on the observed treatment estimates will then be assessed by estimating treatment effect bounds for samples with non-random sample selection/attrition as proposed by Lee [47]. Using this approach we are able to infer whether observed differences between the intervention and control groups can be explained by extreme, non-random sample selection. Depending on these results, missing outcome observations for participants will be imputed based on pre-scores and a set of background characteristics. The quantitative analysis of the primary and secondary endpoints will be performed on an intention-to-treat (ITT) basis following the per-protocol analysis. The primary analysis will be based on ITT. Potential dependency between outcome measures is addressed using multivariate analyses. Potential heterogeneity will be addressed by estimating treatment effects for subgroups (e.g., based on pre-scores). In order to understand the mechanisms by which observed differences are generated, a rich set of analyses is performed based on variation in (1) experiences when using the app (e.g., perceived user friendliness, ecological momentary assessment, cybersickness, VR vs 360°) and (2) intensity of using the app. Per-protocol analysis will be based on two groups: (1) those who returned the post-test and follow-up questionnaires (completers) and (2) those who completed 50% or more of the treatment modules and returned the questionnaires (adherent completers). Comparisons will be made between and within the groups before and after measurements.

Intention-to-treat and per-protocol analysis will be used on continuous scales using regression estimation standardized effect sizes (Cohen’s *d*) and confidence intervals will be calculated. Usage data through the mobile app (anxiety level during VR exposure, time spent in VR, number of VR sessions completed) will be collected during the study to model missing data. SPSS version 21 will be used for the analyses. A *p* value < 0.05 will be considered to indicate statistical significance. All design, implementation, and reporting will be carried out in accordance with Consolidated Standards of Reporting Trials (CONSORT) and Standard Protocol Items: Recommendations for Interventional Trials (SPIRIT) guidelines (Additional file 1) [48–50].

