### Randomization, blinding, and treatment allocation

A randomization list will be created with Random Allocation Software using block randomization of 6, 8, 10, and 12 blocks at an allocation ratio 1:1. Participants will be randomized into two groups: experimental or waitlist condition. The randomization list is kept by an independent researcher. This person reveals the next randomization outcome after every inclusion and thus ensures that the researchers are blind for treatment allocation. Due to the nature of the study, it is not possible to blind the participants for the randomization outcome.

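### The Lee attrition bounds name no role for the baseline AQ; using it would usually narrow them, a modest gain in precision rather than the repair of an error

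*Protocol article*

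**What the plan says.** The Statistical analyses section of the protocol article handles missing outcomes in sequence. A table first compares participants with and without missing outcomes on background characteristics, pre-scores and other covariates. The consequences for the treatment estimate are then assessed by "estimating treatment effect bounds for samples with non-random sample selection/attrition as proposed by Lee [47". The stated purpose is that "we are able to infer whether observed differences between the intervention and control groups can be explained by extreme, non-random sample selection". Whether missing outcomes are then imputed, from pre-scores and background characteristics, depends on these results. Subgroups may also be formed on pre-scores.

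Pre-scores are thus named for the table, the imputation and the subgroups. The sentences on the bounds name no covariate. They neither say that the bounds will be unadjusted nor rule out adjustment.

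The Acrophobia questionnaire section says of the AQ: "Both subscales will be taken at baseline, directly after finishing the modules, at post test, and at follow-up". Under Procedure, participants are allocated only after completing the online battery, so the baseline AQ precedes randomisation. On loss, the Sample size section says: "With an anticipated dropout of 40%, this requires a total target sample size of 180 participants". It gives no figure by arm.

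**The concern.** Lee bounds trim one tail of the outcome distribution in the arm with the higher response rate, so their width grows with the spread of the outcome. On the unadjusted AQ that spread includes the between-person variation that the baseline AQ already predicts. Because baseline is fixed before allocation, subtracting a common baseline prediction from every outcome leaves the effect among those who would respond in either arm unchanged. The bounds then target the same quantity with less spread to trim.

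This matters because the article gives the bounds a deciding role: they settle whether selection could explain the result, and they bear on whether outcomes are imputed. Unequal loss is plausible from the design. The waitlist gains access to the app only after completing the post test, an incentive that the app arm lacks. If the bounds are wider than necessary, the plan may leave open a question that its own data could have narrowed.

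**Working it through.** **The plan's own figure.** The design assumes an effect "of 0.50 (two-sided), an alpha of 0.05 and statistical power" "of 0.80, we need 64 participants in each condition (128 participants in total". A t-test calculation gives 63.8, so 64 per arm: reproduced. The target of 180 corresponds to 128 × 1.4 = 179.2. Dividing by the 60% retained would give 128 / 0.6 = 213.3, so 214. That is a separate matter and is not used below.

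**Inputs from the article.** d = 0.50; 180 randomised "at an allocation ratio 1:1", so 90 per arm; 40% loss overall.

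**Inputs assumed.** Split of the 40% by arm; normal outcome with SD 1; loss at random within arm; correlation r between baseline and post-test AQ of 0.4 to 0.7. The article gives neither the split nor r.

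**Formulas.** Let q1 and q0 be the response rates in the app and waitlist arms, with q0 the higher.

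- Trimmed share: p = (q0 − q1) / q0
- Shift of the trimmed mean: s = φ(c) / (1 − p), with c = Φ⁻¹(1 − p)
- Unadjusted bounds: 0.50 ± s
- Baseline-adjusted bounds: 0.50 ± s√(1 − r²)

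Example, 50%/30% loss: p = (0.70 − 0.50) / 0.70 = 0.286; s = 0.476; lower bound 0.50 − 0.476 = 0.024. At r = 0.6 the factor is √0.64 = 0.8, so the lower bound is 0.50 − 0.381 = 0.119.

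**Expected lower bound (SD units)**

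| Loss app / waitlist | p | s | Unadjusted | r = 0.4 | r = 0.6 | r = 0.7 |
|---|---|---|---|---|---|---|
| 40% / 40% | 0 | 0 | 0.50 | 0.50 | 0.50 | 0.50 |
| 45% / 35% | 0.154 | 0.280 | 0.22 | 0.24 | 0.28 | 0.30 |
| 50% / 30% | 0.286 | 0.476 | 0.02 | 0.06 | 0.12 | 0.16 |
| 55% / 25% | 0.400 | 0.644 | −0.14 | −0.09 | −0.02 | 0.04 |

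The width falls by 1 − √(1 − r²): 8%, 20% and 29% at r = 0.4, 0.6 and 0.7.

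**What drives the lower bound to zero.** Unadjusted, it reaches zero at a gap of about 21 points (50.7% against 29.3%). With baseline used, the gap needed is about 26 points at r = 0.5 and 34 points at r = 0.7.

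**A few strata suffice.** At 50%/30% loss, trimming within 3 to 5 baseline strata gives a lower bound of about 0.08 at r = 0.5 and 0.13 to 0.15 at r = 0.7. Very fine strata give 0.09 and 0.16.

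**Sampling variation (simulation, 90 per arm, 50%/30% loss).** The estimated lower bound exceeds zero in about 56% of trials unadjusted, and in about 64%, 76% and 83% adjusted at r = 0.4, 0.6 and 0.7. If it must exceed zero by 1.96 standard errors, the shares are 3% unadjusted and 10% adjusted at r = 0.6. At 45%/35% loss they are 16% and 32%.

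**Loss that is not random.** Two checks point in different directions. With 50%/30% loss depending on baseline and outcome (r = 0.6, true effect 0.50), the unadjusted bounds were −0.02 to 0.92 and the adjusted ones 0.05 to 0.78. With non-random loss, a truncated baseline and r = 0.4, the adjusted bounds were hardly narrower and their lower limit was below the unadjusted one (0.22 against 0.27).

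**The case against.** The strongest objection is that this rests on silence. The article is condensed, a fuller analysis plan may exist, and covariates for a sensitivity bound are the kind of detail left to it. A reader might infer that the plan excludes baseline from the bounds; the text does not say so. This stands, and it is why the point is a recommendation on a named method and not a defect. It is still worth making, because the same section says where pre-scores will be used and the bounds are not among those places.

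A reader might also infer that 40% dropout, or leaving out baseline, is what brings the lower bound to zero. Neither does. With equal 40% loss nothing is trimmed and the bound stays at 0.50. A gap of about 20 points between arms is needed, and the article gives no split.

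The AQ-Anxiety entry threshold truncates the baseline range and tends to lower r, so the smaller gains at r = 0.4 deserve weight. Nor is the adjusted lower limit always the higher one: in simulated trials at r = 0.6 it fell below the unadjusted limit in 24% (50%/30% loss) and 33% (45%/35%). This too stands. It argues for fixing in advance which version decides.

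Finally, unadjusted bounds are valid and the primary intention-to-treat estimate is unaffected. Both are true.

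**Conclusion.** The point holds as an optional but worthwhile gain in precision. The bounds carry a decision in this plan, the baseline AQ is available on everyone before allocation, and the article assigns it no role in them.

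The gain in the expected lower bound is 0.02 to 0.08 SD at 45%/35% loss and 0.04 to 0.14 SD at 50%/30% loss. This rests on d = 0.50, a normal outcome, loss at random within arm, an assumed split of the 40%, and an assumed r of 0.4 to 0.7. Gaps much beyond 20 points can still take the adjusted bound to zero or below, and under strongly outcome-dependent loss the gain can disappear.

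The documents do not support the stronger reading that the planned bounds are wrong or cannot serve their purpose.

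**What to change.** State in the Statistical analyses section that the Lee bounds will be tightened with the baseline AQ. This can be done by trimming within a few prespecified baseline AQ strata, or by trimming post-test AQ minus its prediction from baseline AQ with one common slope. Say in advance which version decides whether selection could explain the arm difference, and report the unadjusted bounds beside it.

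The cost is a short addition to the text and slightly more analysis work, with no new data or participants. The downside is that in a given sample the adjusted lower limit may be below the unadjusted one, and the prespecified version would then have to stand.
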